# Liver resection surgery versus thermal ablation for colorectal LiVer MetAstases (LAVA): study protocol for a randomised controlled trial

**DOI:** 10.1186/s13063-018-2499-5

**Published:** 2018-02-13

**Keywords:** Randomised controlled trial, Cost-benefit analysis, Liver, Neoplasm metastasis, Colorectal neoplasms, Hepatectomy, Ablation techniques

## Abstract

**Background:**

Although surgical resection has been considered the only curative option for colorectal liver metastases (CLM), thermal ablation has recently been suggested as an alternative curative treatment. A prospective randomised trial is required to define the efficacy of resection vs ablation for the treatment of colorectal liver metastases.

**Methods:**

*Design and setting:* This is a multicentre, open, randomised controlled non-inferiority trial design with internal pilot and will be performed in tertiary liver centres in UK and The Netherlands.

*Participants:* Eligible patients will be those with colorectal liver metastases at high surgical risk because of their age, co-morbidities or tumour burden and who would be suitable for liver resection or thermal ablation.

*Intervention:* Thermal ablation as per local policy.

*Control:* Surgical liver resection performed as per centre protocol.

*Co-interventions:* Further chemotherapy will be offered to patients as per current practice.

*Outcomes*

Pilot study: Same as main study and in addition patients and clinicians’ acceptability of the trial to assist in optimisation of recruitment.

Primary outcome: Disease-free survival (DFS) at two years post randomisation.

Secondary outcomes: Overall survival, timing and site of recurrence, additional therapy after treatment failure, quality of life, complications, length of hospital stay, costs, trial acceptability, DFS measured from end of intervention.

*Follow-up:* 24 months from randomisation; five-year follow-up for overall survival.

*Sample size:* 330 patients to demonstrate non-inferiority of thermal ablation.

**Discussion:**

This trial will determine the effectiveness and cost-effectiveness of thermal ablation vs surgical resection for high-risk people with colorectal liver metastases, and guide the optimal treatment for these patients.

**Trial registration:**

ISRCTN Registry, ISRCTN52040363. Registered on 9 March 2016.

**Electronic supplementary material:**

The online version of this article (10.1186/s13063-018-2499-5) contains supplementary material, which is available to authorized users.

## Background

### Colorectal liver metastases

Bowel cancer (colorectal cancer) is the UK’s second biggest cancer killer and the fourth most common cancer. Over 41,000 people are diagnosed with bowel cancer each year in the UK and about 34,000 in England alone. Just under 16,000 colorectal cancer patients die each year in the UK, equating to one death every 32 min [1, 2]. About 20% of patients have liver metastases at presentation [3] and another 30% subsequently develop liver metastases [4]. The resection of colorectal liver metastases (CLM) has provided a good long-term survival for many patients who would have previously been treated with palliative therapy alone [5–8]. However, only about 7–20% of people with CLM undergo potentially curative liver resection because of the age and co-morbidities of the patient or because of the extent of cancer spread [7]. Increasing the number of patients who can undergo potentially curative therapy for liver metastases alone is a main NHS goal for improving the outcome for bowel cancer patients in the UK. Therefore, specialist liver resection centres are carrying out more extensive and complex resections including elderly patients with major co-morbidity. This more extensive surgery in patients with co-morbidity is associated with an increased morbidity and mortality (high-risk patients) [9–14].

### Thermal ablation

Thermal ablation is an alternative modality for treatment of CLM and involves destruction of cancer by heat. Thermal ablation includes established modalities such as radiofrequency ablation (RFA) or microwave ablation (MWA).

#### Radiofrequency ablation

RFA involves localised destruction of the tumour using heat generated by high-frequency alternating current to produce coagulative necrosis of the tumour [15]. For the treatment of CLM, it is generally carried out as a short-stay procedure under general anaesthesia, although it can also be performed under local anaesthesia in some patients [15]. Multiple sessions may be required to treat all the tumours in some patients. It can be performed percutaneously under image guidance (usually CT scan) but can also be performed by open or laparoscopic surgery [15]. Contraindications for RFA include lesions close to the hepatic hilum or adjacent to the hepatic duct as injury may lead to delayed stenosis of the duct and lesions abutting the bowel because of the risk of perforation [15]. Lesions near large blood vessels are often difficult to treat because of dissipation of heat by circulation [15]. According to the Cardiovascular and Interventional Radiological Society of Europe (CIRSE) criteria, RFA is recommended for CLM only when there are ≤ 5 lesions and tumour size does not exceed 3 cm at its longest axis [16]. The dose delivered for RFA varies from one patient to another and is guided by the ablation zone diameter. The target is to heat the tissue to 60 °C at which coagulative necrosis occurs but keep the electrode tip temperature < 100 °C to avoid charring and vaporisation of tissue [15].

#### Microwave ablation

MWA involves localised destruction of the tumour using heat generated by microwave [17–19]. For the treatment of liver lesions, it is usually carried out as a short-stay procedure under general anaesthesia as with RFA, although it can also be performed under local anaesthesia in some patients [17]. As with RFA, multiple sessions may be required in some patients to treat all the lesions (index disease). It is usually performed percutaneously under image guidance (usually ultrasound scan) [17]. It is more effective than RFA in lesions near large blood vessels [17–19]. Major technical limitations of MWA include low power, shaft heating, large diameter probes, long and relatively thin (1–2 cm) ablation zones, and unpredictability regarding the size and shape of the zone of ablation [17].

#### Effectiveness of ablation methods

These methods are currently used for patients with CLM not suitable for surgical resection [20] and not for patients with a possibility of curative liver resection surgery because of high local recurrence rates with thermal ablation [21]. Multiple studies have highlighted the superiority of surgery to ablation for preventing recurrence within the liver [21, 22]. A recent series from Nishiwada et al. showed a 13% recurrence after surgery as opposed to 46% after thermal ablation [21]. Other newer modalities of thermal ablation include laser ablation and high-intensity focused ultrasound (HIFU) [23, 24]. Thermal ablation may be associated with a lower chance of cure than surgery because of the problem with local recurrence. To determine the evidence for thermal ablation, a National Institute for Health Research (NIHR) Health Technology Assessment (HTA)-funded systematic review of literature was commissioned and subsequently published in February 2014 [25]. The systematic review identified one non-randomised comparative study in which the survival in patients with RFA was similar to liver resection surgery despite the RFA group having more co-morbidities or more extensive liver metastases [26]. An exploratory cost-effectiveness analysis performed by the group based on this non-randomised study showed that RFA has the potential to be cheaper and might result in better health-related quality of life. Another non-randomised study published since this systematic review has also shown that patients undergoing RFA have survival comparable to surgery despite having more extensive liver metastases [22]. Similarly, an underpowered randomised controlled trial (RCT) showed no evidence of difference in survival between MWA and liver surgery in resectable CLM [27]. However, in another non-randomised study published after the systematic review by Loveman et al., people who were eligible for surgery but preferred RFA had poorer survival than those undergoing surgery [28].

#### Comparison of methods of thermal ablation

Non-randomised studies comparing MWA with RFA suggested that MWA is better than RFA in terms of technical feasibility and lower disease recurrence in patients with unresectable CLM [25]. Of the newer forms of ablative methods, such as HIFU, CyberKnife®, and cryotherapy, there are no publications comparing these newer ablation methods with either RFA or MWA. In reality, different surgeons and radiologists have their own preferences of method of ablation because of this uncertainty.

### Potential advantages of thermal ablation over surgery

Current evidence suggests that thermal ablation has lower complication rates and better health-related quality of life than surgery [25, 29]. Thermal ablation is also less expensive than liver resection [25], which will result in cost savings to NHS. Ablation therapy has the potential to decrease the pain after treatment and time taken for recovery from cancer therapy which will decrease the number of work days lost by the patient and relatives.

### Potential concerns about thermal ablation compared with surgery

The major concern about thermal ablation is the high incidence of local recurrence and extrahepatic recurrence [29]. As a result, it would be anticipated that it will not offer similar cancer-related outcomes as liver resection surgery [29]. However, in patients who are at high surgical risk but would currently be considered for liver resection [30], the short- and long-term outcomes after surgery are poorer than the normal surgical cohort [9–14] and hence thermal ablation may be a valid alternative to surgery for this group.

### Uncertainty in treatment of patients with potentially resectable colorectal liver metastases

The HTA review suggested that there is equipoise regarding treatment using ablation or surgery of elderly patients and those with significant co-morbidities which pose significant risk from a surgical procedure and that good quality evidence of both the clinical benefit and cost-effectiveness of ablation is required [25]. In summary, liver resection is a modality with higher short-term mortality and complication rates and poorer quality of life during the first 3–6 months but with low local recurrence rates and a high potential for cure: > 25% of patients are alive five years after liver resection of CLM [31]; ablation is a less expensive modality with practically no short-term mortality, lower complication rates, earlier recovery, and higher short-term quality of life but with high local recurrence rates and the crucial uncertainty of whether it could offer similar long-term cancer-related outcomes as liver resection [30]. From a practical aspect, the choice in the treatment of patients with potentially resectable CLM lies between these two modalities.

### When can one consider ablation to be equivalent to liver resection in terms of long-term results?

Liver resection for CLM is a major surgical procedure and carries a postoperative mortality of approximately 3–4% and a complication rate of ~ 40% [31]. Because of the effects of major surgery and the associated pain, the patients take about 2–3 months to recover from surgery and the quality of life is only 0.65 on a scale of 0 to 1 (1 indicating perfect health) even six months after liver resection [25]. As the patient group identified for this trial are those considered high-risk in terms of age, co-morbidity and the extent of liver resection required, the mortality, morbidity and length of hospital stay are likely to be considerably higher than the average and the health-related quality of life and recovery period significantly greater.

In contrast, the ablative methods have fewer complications (6%) [26] and the quality of life is 0.74 (on a scale of 0 to 1) by three months [25]. An informal discussion with patient representatives from Bowel Cancer UK suggested they were willing to trade-off 3–6 months (average 4 months) of their long-term survival in return for a less-invasive procedure with significantly lower complication rates compared to surgery. So, on average, the long-term results of ablation and surgery can be considered equivalent if the difference in long-term survival between the modalities is < 4 months. Clearly, if ablation results in similar or better survival, ablation is the better option since it is less invasive and results in better quality of life in the short-term.

### Choice of patient group to be investigated

There has been no adequately powered RCT comparing ablation vs surgery in patients with CLM. Retrospective cohort studies highlight the high local recurrence rate associated with thermal ablation in comparison to liver resection surgery but a much lower procedure-related morbidity and mortality [21, 22]. The options include performing a RCT for low-risk patients (young patients without co-morbidities with limited extent of cancer spread) with CLM, high-risk patients with CLM, or all patients with CLM who are suitable for undergoing liver resection. There is good long-term data on the efficacy of surgical resection. Surgical resection provides low rates of local recurrence and disease-free survival (DFS) proportions of ~ 28% [31]. However, there is a high rate of local recurrence following thermal ablation and a lack of long-term data on the efficacy of ablation in patients with CLM. Because of the known rates of local recurrence and the lack of long-term data on cancer outcomes, the majority of clinicians feel that it is unethical to randomise low-risk patients to ablation or surgery despite the short-term benefits of lower complication rates, less pain and lower costs in patients undergoing ablation.

While some non-randomised studies did not justify these concerns and demonstrated equivalent survival between RFA and liver resection despite patients undergoing RFA having more co-morbidities or more extensive cancer [22, 26], another non-randomised study supported these ethical concerns and demonstrated that RFA had poorer five-year survival compared to surgery, the only difference between the patient groups in the second study being their preference for RFA or surgery [28].

However, with high-risk patients, there is significant uncertainty as to the benefits of surgery and the majority of clinicians feel that there is equipoise between these modalities for this patient group. These patients have 1.5–2 times lower survival than low surgical risk patients [12–14]. In this research, we will compare the effectiveness and cost-effectiveness of ablation vs surgery in this high-risk group of patients. If this research shows equivalent results of thermal ablation and surgery in this group, this will provide justification for a subsequent clinical trial on low-risk patients.

### Aim

The aim of this research is to compare the effectiveness and cost-effectiveness of thermal ablation vs liver resection surgery in high-risk patients with CLM.

## Methods

The trial has been registered in ISRCTN and can be accessed at http://www.isrctn.com/ISRCTN52040363. The SPIRIT (Standard Protocol Items: Recommendations for Interventional Trials) for this research is available in Additional file 1 [32].

### Design

A prospective, multicentre, open, pragmatic parallel randomised controlled non-inferiority trial design with internal pilot to investigate the effectiveness and cost-effectiveness of ablation (RFA or MWA) compared to liver resection for the treatment of patients with resectable CLM who would be considered high-risk for surgery and with a low chance of cure. The internal pilot will provide information about the feasibility of recruitment with a qualitative sub-study exploring the reasons why potential participants agree or do not agree to take part in the trial and methods of communication about the trial. The standard of surgical resections and thermal ablation procedures will be monitored during the internal pilot, along with assessment of data quality for key fields. Findings from the pilot will inform whether any changes are required to the trial design.

### Setting/context

Participating sites will be tertiary liver, pancreatic and gallbladder (HPB) centres. The trial will open in at least 20 research sites throughout the UK and the Netherlands. It is anticipated that at least four patients per site per year will be randomised into the trial, allowing the sample size of 330 patients to be recruited over a four-year period. In the 12-month pilot, we would expect at least 45 patients to be randomised with at least 15 sites open to recruitment to establish the feasibility of recruitment required for the main trial.

### Eligibility criteria for surgeons and radiologists

All surgeons and radiologists involved in the trial will have prior experience of performing relevant (resection or ablation) procedures for a minimum of 20 patients with liver cancer. The minimum standards to be achieved during the trial were discussed in the pre-trial standardisation meetings. Ablation therapy during open or laparoscopic surgery could be performed by either a radiologist or surgeon with sufficient experience.

### Sample size calculations

A total of 330 patients are required to demonstrate non-inferiority (non-inferiority margin of four months) of thermal ablation with respect to resection in terms of DFS with 80% power at the 2.5% one-sided level of significance, allowing for a four-year accrual period, two-year follow-up, and assuming 14 months DFS in the resection arm and allowing for a 5% drop-out rate.

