### Post-treatment care

Participants will be reviewed in clinic at 3, 6, 12, 18 and 24 months post randomisation. Follow-up imaging investigations (CT scan chest, abdomen and pelvis minimum) and tumour markers will be performed following completion of successful treatment of the index disease until disease recurrence.

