‘NHS England Strategic and Operational Planning 2014 to 2019’ states the following ‘The healthcare system is facing the challenge of significant and enduring financial pressures. People’s need for services will continue to grow faster than funding, meaning that we have to innovate and transform the way we deliver high quality services, within the resources available, to ensure that patients, and their needs, are always put first.’ Clearly, it is important to maximise the health of people using the resources available.

This research will achieve this purpose of maximising the health of people using the resources available. The results of this research can be adopted immediately in the UK because of widespread availability of expertise in both thermal ablation techniques and liver resection surgery, resulting in maximisation of the health benefits using the resources available in a short period of time for high-risk patients with potentially resectable CLM. This research may also have indirect benefit for low surgical risk patients with CLM in the long term. The results of the current research will either justify the concerns of clinicians who consider that thermal ablation is inferior to surgery for the treatment of patients with CLM (in which case, no RCT comparing ablation and surgery will be conducted in low surgical risk patients as it is extremely unlikely that ablation is equivalent or better than surgery in low surgical risk patients if it offers worse results than surgery in high surgical risk patients) or it may reassure clinicians that ablation is an effective therapy in which case, a subsequent RCT may be conducted in low surgical risk patients.

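### The 330 patients give 80% power only if DFS is followed to a common closing date; with the 24 months per patient that the protocol describes, power is about 70%

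*Protocol article*

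**What the plan says.** **Sample size calculations.** The 330 patients rest on a "non-inferiority margin of four months" and on 5% drop-out, and are said to give "80% power at the 2.5% one-sided level of significance, allowing for a four-year accrual period, two-year follow-up, and assuming 14 months DFS" on resection. The section does not say whether 14 months is a median or a mean, on what scale the margin is tested, or how many events are expected.

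**Follow-up and endpoint.** Several sections place the DFS horizon at two years for each patient:
- Abstract, Follow-up: "24 months from randomisation; five-year follow-up for overall survival".
- Post-treatment care: "Participants will be reviewed in clinic at 3, 6, 12, 18 and 24 months post randomisation".
- CT scan central review: the follow-up scans listed for checking recurrence end at around 24 months.
- Primary endpoint: DFS two years after randomisation.
- Longer-term follow-up: only survival is obtained later, from national statistics.

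The Statistical analysis section plans a survival model. It censors patients with no event reported in their trial follow-up at the date they were last known to be event-free.

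**The concern.** The power of a time-to-event comparison depends on the number of events. Accrual length enters such a calculation only if early patients are followed longer than late ones. If each patient had a fixed 24 months, the four-year accrual period would play no part. Naming it therefore suggests that DFS events between months 24 and 72 were counted on, whereas the rest of the protocol describes DFS assessment ending at month 24.

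If those later events are not collected, the trial has fewer events than its power claim needs. With truly equal treatments, the chance of failing to show non-inferiority would be about 30% instead of the planned 20%.

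**Working it through.** **Inputs from the protocol.** One-sided 2.5%, 80% power, 14 months DFS on resection, four-month margin, 48 months of accrual, 24 months of follow-up, 5% drop-out, 330 patients allocated 1:1.

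**Assumptions the protocol does not state.** 14 months is a median; DFS is exponential; the margin is a hazard ratio of 14/(14 − 4) = 1.40 with a true ratio of 1; accrual is uniform.

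**1. Events needed (Schoenfeld).**
4 × (1.960 + 0.842)² / (ln 1.4)² = 277.3 (Freedman: 283).

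**2. Reproducing 330 with a common close.** With λ = ln 2 / 14 = 0.0495 per month and follow-up spread evenly from 24 to 72 months:
- P(event) = 1 − (e^(−24λ) − e^(−72λ)) / (48λ) = 1 − (0.3048 − 0.0283) / 2.377 = 0.884
- 277.3 / 0.884 = 313.8 evaluable patients
- 313.8 / 0.95 = 330.3 randomised

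At 330 × 0.95 = 313.5 evaluable patients this gives 277 events and 80.0% power, so the stated figure is recovered.

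**3. The same 330 with DFS observed for 24 months each.**
- P(event) = 1 − e^(−24λ) = 0.695
- 313.5 × 0.695 = 218 events, 59 fewer than needed
- Power = Φ(√(218/4) × ln 1.4 − 1.960) = Φ(0.524) = 70.0%

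Simulating a Cox model gave 69% at 157 per arm and 73% at 165 per arm under the 24-month limit. Under a common close it gave 80% and 81%.

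**4. Sensitivity of the 24-month result.**

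| Variant | Power |
|---|---|
| Schoenfeld, 5% drop-out | 70.0% |
| Freedman, 5% drop-out | 69.2% |
| No drop-out (330 evaluable, 229 events) | 72.2% |
| Loss at 5% per year applied to 313.5 patients | 68.2% |
| Event rates at 14 v 10 months, 5% drop-out | 73.4% |
| Event rates at 14 v 10 months, no drop-out | 75.6% |
| 14 months as a mean, with and without drop-out | 77.0% and 79.0% |

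**5. Which reading fits 330?** With medians, a common close gives 321 to 338 patients across Schoenfeld and Freedman and both sets of event rates. A 24-month limit gives 389 to 429, and about 420 on the formula of step 2. Reading 14 months as a mean gives about 308 to 314 with the stated accrual plus follow-up, and about 356 to 364 with a 24-month limit. Only the median with a common close lands on 330.

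**The case against.** **The assumptions are inferred.** The protocol states neither median nor exponential nor hazard-ratio margin, and 330.3 comes from one variant with unrounded events. This stands, and it is why the result needs a range. It does not rescue the 80%, because no variant tried reaches it under 24-month follow-up.

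**The 24-month limit is also inferred.** No sentence says DFS is administratively censored at 24 months, and Post-treatment care continues imaging until recurrence with no end date. A reader might conclude that later events certainly will not be observed, but the document does not go that far. It does schedule no visit after 24 months, fix the endpoint at two years and reserve longer follow-up for survival. The sections therefore need reconciling.

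**Treatment failures are set to time 0.** This adds early events at a rate the protocol does not give. Assumed failure rates of 5%, 10% or 20% in both arms, each counted as a full event, give about 71%, 72% or 74% power.

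**The exponential tail may be wrong.** The section on choice of patient group cites DFS of about 28% after resection, with no horizon given and in a general resection population. If that were a plateau, at most 0.72 × 313.5 ≈ 226 patients would ever have an event. High-risk patients may do worse, so this is uncertain. It stands as a warning that a common close might not restore 80%, and that a fixed target near 278 events might never be reached.

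**Two further inferences are not supported.**
- A reader might take "allowing the sample size of 330 patients to be recruited over a four-year period" as an arithmetic error, since 20 sites × 4 per year × 4 years = 320. The site and patient numbers are all given as minimums, so 320 is a floor and contradicts nothing.
- A reader might take the Discussion's "The results of the current research will either justify the concerns of clinicians who consider that thermal ablation is inferior to surgery" and its alternative to mean that an inconclusive result would be declared inferiority. That is discussion prose and not a decision rule. The analysis section reports 95% confidence intervals, which would show an inconclusive result as such.

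**Conclusion.** The point holds as an inconsistency between the basis of the sample size and the described DFS follow-up. Under the reading that reproduces 330, the stated 80% belongs to a design with 24 to 72 months of DFS follow-up. With 24 months per patient, power is about 70%. Across the median-based variants the shortfall is 4 to 12 percentage points. The mean reading shrinks it to 1 to 3 points but does not reproduce the sample size.

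The conclusion rests on exponential DFS, a hazard-ratio margin of 1.40, uniform accrual and equal true effects. It concerns power only: the type I error and the four-month margin are unaffected.

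**What to change.** Reconcile Sample size calculations with the abstract, Post-treatment care and Primary endpoint in one of two ways.

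1. **Keep 24-month DFS.** State whether 14 months is a median or a mean, give the margin as a hazard ratio, give the expected events (about 218) and restate the power as about 70%, with its range. The cost is one corrected paragraph and a less favourable figure.
2. **If DFS was meant to run to a common closing date,** say so in the endpoint and follow-up sections, and describe how recurrence will be dated after the last scheduled visit. No patients are added. It does change the stated two-year endpoint, and it needs up to four more years of recurrence follow-up for the earliest patients in an unblinded trial. The 80% would still depend on events continuing to accrue after month 24, so that assumption should be stated too.
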